| STATISTICAL ANALYSIS | **Descriptive statistics**  **Comparison of groups**  The trial being a non-inferiority trial, the main analysis will be a per-protocol analysis to be conservative by increasing the contrast between the groups.  Main objective  The active spa therapy will not be considered inferior to the standard spa therapy if the lower bound of the confidence interval at 90% of the difference between the 2 groups (active spa therapy minus standard spa therapy) for the main outcome criterion (percentage of respondents according to the composite criterion) is not less than 15%. After verification of the randomization that could be unbalanced due to the Zelen randomization mode, the final analysis will be adjusted if necessary on the variables that differ between the 2 groups.  Secondary objectives  - The same analyses will be repeated for the MCII composite criterion, pain and function at 3 months, and PASS criteria.  - To determine the predictive factors of spa therapy response, a bivariate analysis will be performed using chi-square tests (or Fisher exact tests depending on the number) for discrete variables and Student t-tests, ANOVA or Wilcoxon tests for quantitative variables. The parameters significant on bivariate analyses (at the conservative threshold of p=0.1) will then be introduced into a stepwise multiple logistic regression.  P<0.05 will be considered statistically significant.  The statistical analysis will be carried out by the Centre for Clinical Epidemiology by using SAS v9.2 (SAS Inc., Cary, NC). |
| EXPECTED FALLBACK | To be able to offer different types of spa therapy in order to adapt to patients' preferences.  Propose a spa therapy that can be performed externally near the patient’s home.  Offer a less tiring cure.  Obtaining thermal approval for the Nancy Thermal site. |

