**4. STUDY DESIGN**

This is a single-centre, randomized, single-blind clinical trial of non-inferiority comparing "standard spa therapy" and "active spa therapy" in knee OA.

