**9. STATISTICS**

**Number of subjects required**

- Main objective: with a 50% percentage of responders to standard spa therapy at 6 months [1], a power of 80%, and an alpha risk of 5%, 135 patients per group are required to significantly demonstrate the non-inferiority of the active spa therapy with a lower confidence limit of the difference in proportions of 15%. Considering that the number of patients lost to follow up may be limited to 5%, a total of 284 patients should be included in the trial.
- For the secondary objective of comparing 3-month responders, the percentage of responders being higher than at 6 months, the number of subjects needed is lower: with a 60% percentage of responders to standard spa therapy at 3 months, a power of 80%, an alpha risk of 5%, 77 patients per group are required to significantly demonstrate the non-inferiority of the active spa therapy with a lower confidence limit of the difference in proportions of 19%. For demonstrating an effect of spa therapy sufficient to obtain thermal approval, the evidence of an effect size of 0.3 in an analysis of the before-and-after effect in the same group [6] with 80% power and 5% alpha risk with a test, 90 patients are needed in each group.

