**Comparison of groups**

The trial being a non-inferiority trial, the main analysis will be per protocol to be conservative by increasing the contrast between the groups.

Main objective

The active spa therapy will not be considered inferior to the standard spa therapy if the lower bound of the confidence interval at 90% of the difference between the 2 groups (active spa therapy minus standard spa therapy) for the main outcome criterion (percentage of respondents according to the composite criterion) is not less than 15%[1]. After verification of the randomization that could be unbalanced owing to the Zelen randomization mode, the final analysis will be adjusted if necessary on the variables that differ between the 2 groups.

Secondary objectives

- The same analyses will be repeated for the MCII composite criterion, pain and function at 3 months and for PASS criteria.

- To determine the predictive factors of spa therapy response, a bivariate analysis will be performed using chi-square tests (or Fisher exact tests depending on the number) for discrete variables, and Student t-tests, ANOVA or Wilcoxon tests for quantitative variables. The parameters significant on bivariate analyses (at the conservative threshold of p=0.1) will then be introduced into a stepwise multiple logistic regression.

A value of p<0.05 will be considered statistically significant.

The statistical analysis will be carried out by the Centre for Clinical Epidemiology by using SAS v9.2 (SAS Inc., Cary, NC).

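### The primary non-inferiority rule has lost its minus sign: as written, active spa therapy must beat standard by at least 15 points at the lower confidence bound

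*Protocol*

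**What the plan says.** Section 4 of the Protocol sets the design: "This is a single-centre, randomized, single-blind clinical trial of non-inferiority comparing" standard and active spa therapy. The primary outcome is the percentage of responders at 6 months, so a higher value is better.

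Section 9, Comparison of groups, Main objective, gives the decision rule. It uses "the lower bound of the confidence interval at 90% of the difference between the 2 groups", and active therapy is not considered inferior if that bound, for "active spa therapy minus standard spa therapy) for the main outcome criterion (percentage of respondents according to the composite criterion) is not less than 15" percent. The Statistical analysis entry of the Summary (section 1) repeats the rule with the same direction of subtraction and the same unsigned figure: "for the main outcome criterion (percentage of respondents according to the composite criterion) is not less than 15" percent.

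The sample-size paragraph of section 9 plans "with a 50% percentage of responders to standard spa therapy at 6 months", then states "a power of 80%, and an alpha risk of 5%, 135 patients per group are required" to show non-inferiority "with a lower confidence limit of the difference in proportions of 15" percent. The Summary's sample-size entry gives the same unsigned limit. No part of the document prints −15%, and none defines 15% as an absolute margin.

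**The concern.** Once the difference is fixed as active minus standard, a negative value means active therapy is worse. A non-inferiority boundary that tolerates a loss of up to 15 points must therefore lie at −15. The rule places it at +15. Read literally, active therapy must be better than standard by at least 15 points even at the lower end of the interval.

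This rule alone decides the primary objective, and it disagrees with both the design label and the sample size. A result that meets the intended criterion would formally fail the protocol, and someone would have to reinterpret the boundary with the data in hand. The problem also spreads: section 9 repeats the same analyses for the 3-month and PASS criteria, and the 19% limit in the 3-month sample-size text is unsigned as well.

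The point is the direction of the threshold. Whether 15 points is a suitable margin is a separate question.

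**Working it through.** **Inputs**
- Standard-arm responders at 6 months: 50% (section 9).
- Active-arm responders: not stated. I assume 50%, a true difference of 0, and show a range below.
- Power 80%, alpha 5%, 135 per group, equal groups (section 9).
- Lower bound of a 90% interval, which is a one-sided 5% test: z = 1.645. For 80% power, z = 0.842.

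**Step 1. Reproduce the planned sample size with the boundary at −15 points**

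Unpooled variance: n = (1.645 + 0.842)² × (0.5×0.5 + 0.5×0.5) / 0.15² = 6.18 × 0.5 / 0.0225 = 137.4, or 138 rounded up.

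Score method (variance under the null restricted to a difference of −0.15, so rates of 0.575 and 0.425): n = [1.645 × √(2 × 0.575 × 0.425) + 0.842 × √0.5]² / 0.15² = 135.3.

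Both are close to the stated 135. One-sided 2.5% would give 175, which does not fit. Allowing 5% loss, 270 / 0.95 = 284.2, in line with the stated 284. The planned size therefore corresponds to a boundary of −15 points with equal rates.

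**Step 2. Chance of meeting each rule with 135 per group**

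The standard error at 50% v 50% is √(0.5/135) = 0.0609. The probability of passing is Φ[(true difference − boundary)/SE − 1.645].

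- Boundary +15, true difference 0: Φ(−0.15/0.0609 − 1.645) = Φ(−4.11) = 0.00002.
- Boundary −15, true difference 0: Φ(+0.15/0.0609 − 1.645) = Φ(0.82) = 0.794.

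Exact enumeration of the two binomials with a Wald 90% interval gives 0.00002 and 0.786.

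With the standard arm at 50% and the SE recalculated for each active-arm rate:

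| True difference (active minus standard) | Rule as written (+15) | Boundary at −15 |
|---|---|---|
| 0 | 0.00002 | 0.794 |
| +5 | 0.0005 | 0.951 |
| +10 | 0.007 | 0.994 |
| +15 | 0.050 | >0.999 |
| +20 | 0.215 | >0.999 |
| +25 | 0.544 | >0.999 |
| +30 | 0.859 | >0.999 |

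The written rule reaches 80% power at a true difference of about +29 points (79% v 50%).

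**Step 3. What has to be observed**

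The half-width of the 90% interval near 50% is 1.645 × 0.0609 = 0.100. The written rule needs an observed difference of about +25 points (slightly less, about +24, when the SE uses the higher active rate). The −15 boundary needs about −5 points or better.

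Take an observed difference of −3 points. The interval is −3 ± 10, or −13 to +7. This fails the written rule and meets the intended one.

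**The case against.** The strongest reply is that this is a dropped minus sign that any statistician would restore. The trial is called non-inferiority throughout, the sample size is meant to show non-inferiority, and the rule itself concludes that active therapy is not inferior. All of this was fixed before any data, so nobody gains a free choice of margin. That is right about intent, and it is why the repair is editorial. It does not make the written criterion correct, and with the sign absent from all four places there is no correct statement to set against the wrong ones.

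Second, the conflict with the stated power depends on the active-arm rate, which the Protocol does not give. This stands as a qualification. If active therapy were 25 to 30 points better, the written rule would often be met. Such a gain is hard to square with a non-inferiority plan, and equal rates come close to reproducing the 135. That match is approximate, since 135.3 rounds up to 136.

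Third, the sign may have been lost when the text was converted. Other symbols are damaged, such as the radiographic grade in section 5.1 and one time limit in section 5.2. This cannot be excluded outright, but loss in four separate places is unlikely.

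Finally, quoting a margin as an unsigned size in sample-size text is common practice. That is fair, so the edits there are mainly for consistency. It does not excuse the decision rule, which compares a signed difference with a number.

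**Conclusion.** The concern holds and must be fixed. As written, the primary rule is a +15-point superiority requirement, and it contradicts the Protocol's own non-inferiority design. In the planning case (50% in both arms, 135 per group) it would be met with probability about 0.00002, against 0.79 for a boundary of −15. The chance stays below 1% up to a true advantage of 10 points. These figures rest on the assumed 50% active-arm rate; that the sign is wrong does not depend on it. The intended boundary is almost certainly −15 percentage points, so this is an error in stating the rule. The sample size is not in question.

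**What to change.** In section 9 (Comparison of groups, Main objective) and in the Statistical analysis entry of the Summary, write: *Non-inferiority is concluded if the lower bound of the two-sided 90% confidence interval of the difference in responder percentage (active minus standard) is greater than −15 percentage points.*

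In both sample-size statements, describe the 15% as a non-inferiority boundary of −15 percentage points and state the active-arm rate assumed. Sign the 19% figure for 3 months in the same way. Because section 9 carries the same analyses over to the 3-month and PASS criteria, also state the signed boundary that applies to each.

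The cost is wording only. The number of patients, the data collected and the analysis method stay as they are.

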**Evaluation of crenotherapy**

Various good-quality thermal therapeutic trials have led to the recognition of spa therapy for treating chronic low back pain [19,20]. Several prospective randomized controlled trials have evaluated the effect of spa therapy for the main indications for crenotherapy in rheumatology: low back pain chronic, hip OA, hand OA, fibromyalgia, rheumatoid arthritis, psoriatic arthritis, spondylitis, chronic neck pain [21–35].

A number of these trials concern, at least in part, knee OA [36–42]. The estimated size effect of the treatment is 0.42, which corresponds to a moderate effect. [36, 39, 40]. In a recent article, Forestier showed in a randomized multicenter study, "Thermarthrosis", the efficacy of a standardized spa treatment protocol in knee OA on pain and function at 6 months [1]. This standardized cure involves 4 thermal treatments (hydrojets, massages, applications of mineral-matured mud at 45°C, balneotherapy) repeated 6 days a week for 3 weeks. The authors showed a symptomatic effect that remained evaluated globally and not according to its different components. This intervention, whose philosophy is based on care at discharge for a load-bearing joint also involves local sedative and anti-inflammatory care.

Although symptomatic efficacy may seem interesting, patients are more likely to sometimes complain about the intensity of this type of care, the fatigue and the difficulties with availability. External care, less intensive at a rate of 3 instead of 6 sessions per week but over a longer period of time, combining standardized spa therapy and rehabilitation, could be an interesting alternative to current conventional treatment. This approach combines the "sedative" action of spa therapy with muscular and proprioceptive strengthening. Indeed, after a sedative phase, it seems logical to recondition the patient for exercise by correcting the proprioceptive disorders and underlying muscle deficiencies, in order to prolong the long-term effectiveness of the spa treatment. However, no study has assessed the value of combining these two therapeutic approaches in knee OA.

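### The primary non-inferiority rule is printed with a limit of 15% where the design and sample size require -15 percentage points

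*Protocol*

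**What the plan says.** Section 4 of the protocol describes a single-blind randomised non-inferiority trial of active against standard spa therapy. The primary outcome is the percentage of responders at 6 months, so a higher value is better.

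The decision rule is in section 9, Comparison of groups, Main objective:

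- The quantity is "the difference between the 2 groups (active spa therapy minus standard spa therapy").
- The statistic compared with the limit is "the lower bound of the confidence interval at 90"%.
- Active spa is not inferior if that bound for the primary outcome ("percentage of respondents according to the composite criterion) is not less than 15%[1"]) satisfies the condition.

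The Statistical analysis row of the summary (section 1) gives the same rule in the same direction, again unsigned: "percentage of respondents according to the composite criterion) is not less than 15"%.

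Section 9, Number of subjects required, sizes the trial for "non-inferiority of the active spa therapy with a lower confidence limit of the difference in proportions of 15"%. Its inputs are 50% responders on standard spa, 80% power, 5% alpha, 135 per group, 5% lost to follow-up and 284 in total. The corresponding row of the summary repeats this. For the 3-month comparison, section 9 gives a limit of 19%, also unsigned. Nowhere is a limit written as negative or described as a tolerated loss.

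**The concern.** On a scale of active minus standard, with more responders being better, a loss for active spa is a negative number. A non-inferiority limit must therefore lie below zero. A lower bound of at least +15 points is a different hypothesis: superiority of active spa by a margin of 15 points.

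This is the only printed success criterion for the primary question. An analyst who applied it as written would almost certainly fail a programme that works exactly as well as the standard. Section 9 also says the same analyses will be repeated for the 3-month responder criteria and for PASS, so the unsigned rule carries over to those comparisons.

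**Working it through.** **Inputs.** From section 9: 50% responders on standard spa, one-sided 5% (the lower bound of a 90% interval), 80% power, 135 per group, 5% loss, 284 in total. Assumption: the true responder rate is also 50% on active spa. The protocol states no true difference; equality is the usual choice for a non-inferiority calculation.

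**1. Reproduce the plan's figure with a limit of -15 points.**

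n = [p₁(1-p₁) + p₂(1-p₂)] × (z₀.₉₅ + z₀.₈₀)² / 0.15²

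= 0.50 × (1.645 + 0.842)² / 0.0225 = 137.4, i.e. 138 per group against 135 stated (2.2% apart).

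With one-sided 2.5% the same formula gives 175, which does not fit. For the total, 270/0.95 = 284.2, which matches 284.

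**2. Power at the stated size.**

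SE = √(2 × 0.25/135) = 0.0609. Half-width of the 90% interval = 1.645 × 0.0609 = 0.100.

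- Limit -15: Φ(0.15/0.0609 - 1.645) = 0.794.
- Limit +15: Φ(-0.15/0.0609 - 1.645) = 0.00002.

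**3. Observed difference needed for success.**

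- Limit -15: -0.150 + 0.100 = -0.050, about -5 points or better.
- Limit +15: 0.150 + 0.100 = +0.250, about +25 points. With standard at 50% and the active arm's own variance at about 74%, the half-width is 1.645 × √((0.25 + 0.19)/135) = 0.094, so about +24.4 points.

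**4. Chance of meeting the printed rule, 135 per group, standard at 50%.**

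| True advantage of active spa | Limit +15 (as printed) | Limit -15 |
| --- | --- | --- |
| 0 | 0.002% | 79.4% |
| +15 points | 5% | over 99.9% |
| +20 points | 22% | over 99.9% |
| +25 points | 54% | about 100% |
| +30 points | 86% | about 100% |

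Under the printed rule, 135 per group reaches 80% power only if active spa is truly somewhere between 25 and 30 points better. The protocol assumes no such advantage.

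**5. The 3-month limit.** The same formula with 60% responders in both arms and a limit of -19 gives 83 per group against 77 stated. That does not reproduce closely, so it is not used as evidence here. For the 3-month comparison the point concerns only the missing sign.

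**The case against.** The strongest reply is that nobody would be misled. The trial is called non-inferiority throughout, and the direction of the difference, the size of 15 points, the 90% interval and the sample size are all prespecified. Only the sign is unprinted. This stands to a large extent: the intent is recoverable. A reader might infer that the primary threshold is open and would become a post-hoc choice once repaired. The documents do not support that, because restoring a sign that the design and the sample size already determine is not choosing a threshold. What remains is that the printed rule cannot be applied as written, and correcting it early avoids any argument.

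A second reply is that the sign was lost in translation or in reading the PDF. Symbols are damaged elsewhere: the Kellgren and Lawrence inclusion criterion has a superscript 3 where another section has ≥, and one < became a letter. The four unsigned places are also near-copies in pairs, not four independent statements. Loss is therefore possible. It is not shown, since ≥ and < survive in other places and the minus is absent in all four. Quoting a margin as a magnitude is common in a sample-size sentence, but it does not work in a rule that fixes the direction of subtraction.

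A reader might also infer that even -15 is too wide, because the rationale section reports "The estimated size effect of the treatment is 0.42, which corresponds to a moderate effect" and a conversion to responder rates would put 15 points near the whole benefit of spa. The documents do not carry that argument. The 0.42 is given without outcome, comparator or time point. One of its cited sources is listed as an open prospective study. Turning it into a rate for a pain, function and surgery composite would rest on an unsupported latent-scale assumption. Section 9 concludes only that active spa is not inferior to standard; it makes no claim of retained efficacy over no spa.

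**Conclusion.** The point holds as an error in the printed decision rule. Read literally, it demands superiority by 15 points: an observed advantage of about 24 to 25 points, and a success probability of about 0.00002 when the arms are equal. The intended rule, with -15, has 79.4% power and needs an observed difference of about -5 points or better. These figures assume 135 evaluable patients per group, 50% responders on standard spa, and a normal approximation with unpooled variance; the power figures also assume equal true rates.

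The sample size is not in error, and the design is not in doubt. The fault lies in the wording of the threshold, but that wording is the only statement of what counts as success on the primary question. It must be corrected.

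**What to change.** - Summary (Statistical analysis) and section 9 (Comparison of groups, Main objective): state that active spa is non-inferior if the lower limit of the two-sided 90% confidence interval for (active minus standard) is greater than -15 percentage points.
- Both sample-size texts (the summary row and section 9): give the limit as -15 percentage points.
- Section 9, 3-month comparison: give the limit as -19 percentage points.

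The changes should be made and dated before any outcome data are seen. They cost a wording amendment only: no change to the number of patients, the visits, the analysis method or the budget.

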# The MCII in OA was determined by Tubach et al. [2]. The MCII is a threshold for improvement that is particularly suitable for therapeutic trials and takes into account that the MCID may be different for an improvement or a worsening. A patient is considered improved if the WOMAC index function subscale score is improved by at least 9.1 from the initial value and/or if the current pain measured on a VAS is improved by at least 19.9 mm. These values correspond to the smallest clinically relevant change for these two outcome criteria [2]. Improvements below this value will be considered treatment failures. Patients with improvement but would still need to have surgery during the study period will also be considered failures. The effect of the two types of spa therapy ("standard spa therapy" and "active spa therapy") for symptomatic knee OA will be assessed by proportion of patients who achieve a composite criterion combining the MCII for pain and/or functional abilities and the absence of knee surgery of the target knee at 6 months.

Secondary criteria

- Percentage of patients reaching the MCII (pain, function and composite score) at the end of the treatment and at 3 months
- Percentage of patients reaching the PASS (pain and function) at 3 and 6 months [14]. The PASS is the value beyond which the patient considers himself/herself to be well. It is defined as for the MCII by the 75th percentile of the score among patients whose assessment of the acceptable symptom state was “good” on a Likert scale with 5 answer modalities. The PASS for WOMAC function is 31 mm and for VAS for pain is 32 mm [14].
- Evolution of quality of life scores (Osteoarthritis Knee and hip Quality of life [OAKHQOL], SF-36) at 3 and 6 months
- Evolution of VAS-fatigue, VAS-pain at 3 and 6 months
- Evolution of WOMAC scores (function) at 3 and 6 months
- Patient satisfaction (overall VAS or heiQ module 9) at 3 and 6 months
- Evolution of drug and care consumption, use of surgery
- 6-minute walking test [43]
- Evolution of posturography parameters: modification of the length travelled and/or the area covered by the pressure centre of the feet after removal or disruption of sensory inputs, somesthesics of balance in distorted visual situations and static and dynamic positions [4]
- Adverse reactions

**4.2. DESCRIPTION OF THE RESEARCH METHODOLOGY, ACCOMPANIED BY ITS SCHEMATIC PRESENTATION SPECIFYING IN PARTICULAR THE VISITS AND EXAMINATIONS PREVUED.**

Collected data

Inclusion visit:

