- Demographics: age, sex, level of education, current or former professional activity, place of residence (size of the municipality)
- Medical history and co-morbidities (Groll functional index)
- Medication
- History of knee OA: initial trauma (rupture of the cruciate ligament knee or lower limb fracture), presence of the symptoms before the current painful episode, duration of the current episode, previous drug treatments (corticosteroid injections, viscosupplementation, symptomatic treatments [analgesics, NSAIDs, symptomatic slow-acting drugs for osteoarthritis" (SySADOA)]) and non-drugs (surgery [osteotomy, arthroscopy, meniscectomy], spa treatment, rehabilitation, other etc.)
- Clinical data: weight, height, static disorders, length inequality of the lower limbs.
- X-rays of < 6 months with weight-bearing, full extended-knee X-ray and Schuss. The radiographs will be digitized for a centralized reading and will be used to confirm the diagnosis of femorotibial OA (Kellgren and Lawrence stage ≥2).
- Posturography examination
- Ultrasound examination

During other visits

Clinical and perceived health data will be collected before the cure (V0), at 3 weeks (V1: end of the standard spa therapy or change of type of care for active spa therapy), at 6 weeks (V2: end of active spa therapy), at 3 months (V3: M3) and 6 months (V4: M6) and will include the following examinations: clinical exam (effusion, joint amplitudes), VAS-pain, VAS-fatigue, WOMAC, OAKHQOL, SF-36, satisfaction, drug consumption, surgery, side effects, posturography examination, 6-minute walk. The number of treatments actually performed by the patients will also be collected.

The assessor will be blinded to the treatment group at 3 and 6 months.

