**4.3. DESCRIPTION OF THE MEASURES TAKEN TO REDUCE AND AVOID BIAS**

Randomization

Most literature reviews emphasize the importance of blinding of the assessor [44,45,46,47] and randomization [48,49,50] in a therapeutic trial. In the context of thermal care, it is impossible to blind the patient, which can lead to a bias of therapeutic preference [51]. The Zelen randomization method (randomization method before consent is obtained) must allow for reducing this bias. This method has been used successfully in the past [52,53]. For some, it has the additional advantage of reducing the number of refusals to enter the study [54]. A review published in 2006 shows that among 58 studies, this method was more frequently used to limit bias than to increase recruitment [55]. This method does not contradict the rules of ethics and is widely used in many studies.

Because patients cannot be completely blinded, randomization will be according to the Zelen method [51]. During the inclusion visit, patients will be informed that the purpose of the research is to study the effectiveness of the care provided during spa therapy. The content of spa therapy will not be explained in detail right away and randomization will occur before consent is obtained. In the event of refusal after allocation of the intervention group (e.g., the patient not wishing to undergo care for 6 weeks), the patient will be assigned to the other group. An information letter and a consent specific to each group will be proposed.

Randomization will be performed centrally and independently by use of a computer program at the Centre for Clinical Epidemiology (CIC EC). The randomization group will be available during the selection visit.

(b) Blinding methods.

The assessor will be blinded to the treatment group at 3 and 6 months.

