**5. INCLUSION AND EXCLUSION OF PEOPLE FROM RESEARCH:**

5.1. INCLUSION CRITERIA

The patients with knee OA:

- Meeting the criteria for knee OA of the ACR (*)
- Uni- or bilateral OA
- Symptomatic: VAS pain > 3 on a scale of 0 to 10
- Radiological femoro-tibial knee OA³ stage 2 of the Kellgren and Lawrence classification
- With consent
- Preliminary medical examination

* The diagnostic criteria used are those of the ACR [Altman 1986]:

- Knee pain and at least 1 of the following three criteria:
  - Age > 50 years old
  - Morning stiffness < 30 min
  - Crepitus on active motion
- The presence of osteophytes on knee X-rays

(sensitivity 94%, specificity 87%)

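### The primary model's covariates are to be picked by which variables are seen to differ, instead of being fixed in advance with the two baseline scores that define the outcome

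*Protocol*

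**What the plan says.** Protocol section 9, Comparison of groups, judges non-inferiority on the lower bound of a 90% confidence interval for the difference in responder proportions, active minus standard, in a per-protocol analysis. The margin is 15 percentage points; I read the bound as -15, since the text omits the sign. It then gives the covariate rule. The reason comes first, "After verification of the randomization that could be unbalanced owing to the Zelen randomization mode", and the consequence follows: "the final analysis will be adjusted if necessary on the variables that differ between the 2 groups". The Statistical analysis row of the summary repeats the rule. No covariate is named in either place.

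The outcome is defined in section 4.1 (and again in 4.8 and 7.1) by change in two scores. For function, the condition is "WOMAC index function subscale score is improved by at least 9.1 from the initial value". For pain, it is a gain of 19.9 mm or more on the VAS. Reaching either one is enough, provided the target knee has had no surgery. Section 4.2 and the follow-up table schedule both scores at V0, before treatment. VAS pain is also taken at the selection visit; WOMAC is not. Entry requires "Symptomatic: VAS pain > 3 on a scale of 0 to 10" (section 5.1).

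Section 4.3 describes randomization before consent. If a patient refuses the allocated group, "the patient will be assigned to the other group".

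**The concern.** A rule of this kind has three weaknesses.

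- **It does not fix the primary model.** Different analysts could check different variables, use different thresholds and arrive at different intervals, each consistent with the protocol.
- **It selects on the wrong property.** A variable matters for precision and bias through its relation to the outcome. An imbalanced but irrelevant variable would enter, while a strong predictor just short of the threshold would not.
- **It leaves out the obvious predictors by default.** The composite is a change from baseline, so the two baseline scores bear on it directly. A patient entering at 31 mm must fall to 31 - 19.9 = 11.1 mm to respond on pain, although the and/or rule still lets that patient respond on function.

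At stake are the credibility of the decisive interval and some precision in a trial planned at 80% power.

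**Working it through.** **The plan's own sample size.** Inputs from section 9: 50% responders (taken as equal in both arms), margin 0.15, power 80%, alpha 5% (one-sided, to match the 90% interval).

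- Variance restricted to the null (0.575 and 0.425): n = [1.645 x sqrt(0.575 x 0.425 x 2) + 0.842 x sqrt(0.5)]^2 / 0.15^2 = 135.3, against 135 stated.
- Simple unpooled formula: n = (1.645 + 0.842)^2 x 0.5 / 0.15^2 = 137.4, so 138.
- Loss to follow-up: 2 x 135 / 0.95 = 284.2, against 284 stated.
- Unpooled power at 135 per group: Phi(0.15 / sqrt(0.5/135) - 1.645) = 79.4%.

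The figure reproduces, and this point does not change it. The design has no spare power.

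**How often chance alone would alter the model.** For k independent variables each tested at level a, P(at least one differs) = 1 - (1 - a)^k. The protocol gives neither k nor a, so a range is shown:

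| k | a = 0.05 | a = 0.10 |
|---|---|---|
| 5 | 23% | 41% |
| 10 | 40% | 65% |
| 15 | 54% | 79% |
| 20 | 64% | 88% |

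These figures assume independence; correlated clinical scores would change them.

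**What a threshold can miss.** With 135 per group, a standardized difference reaches p<0.05 only at about 1.96 x sqrt(2/135) = 0.24 SD. If a score carries an assumed log-odds of 0.4 or 0.7 per SD, an imbalance just below that could shift the risk difference by up to 0.25 x 0.4 x 0.24 = 2.4 points or 0.25 x 0.7 x 0.24 = 4.2 points (0.25 is the steepest logistic slope). The rule would leave that unadjusted.

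**Error rate and power.** Simulation with 12,000 runs per scenario, 135 per group, 50% responders in the standard arm, two baseline scores with log-odds 0.4 or 0.7 per SD, eight unrelated variables, a difference defined as p<0.05, chance imbalance only, and a standardized risk difference with a 90% interval. The prognostic strengths and the number of variables are assumptions, not protocol figures. Results are for log-odds 0.4 / 0.7:

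| Analysis | Type I error at -15 points | Power at true difference 0 |
|---|---|---|
| Unadjusted | 4.65% / 4.8% | 79.0% / 79.2% |
| Adjusted for variables that differ | 4.6% / 4.4% | 79.3% / 80.3% |
| Always adjusted for the two scores | 4.95% / 4.9% | 81.8% / 85.6% |
| Unadjusted or selected, whichever is more favourable | 5.0% / 5.2% | 80.3% / 81.3% |

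Always adjusting gains 81.8 - 79.0 = 2.8 or 85.6 - 79.2 = 6.4 points over no adjustment. The selection rule gains 0.3 or 1.1 points. A smaller separate simulation (1,500 trials, about 53% responders, assumed baseline to 6-month correlation of about 0.5) points the same way. The SD of the risk difference was 0.0614 unadjusted, 0.0601 under selection and 0.0583 pre-specified. With power = Phi(0.15/SD - 1.645), these give 78.7%, 80.2% and 82.3%.

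**The case against.** The strongest defence is that the rule has a reason. It answers imbalance expected from the Zelen design, where refusers change groups by choice and are then analysed per protocol. Adjustment is legitimate there, and a primary model limited to the two outcome scores could leave in place confounding by whatever drives refusal. This stands, and it shapes the fix. It does not rescue the rule: foreseeable imbalance is a reason to name the covariates beforehand, and a check on observed differences can still miss the ones that matter.

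It can also be said that the SAP may supply the details, and that leaving out prognostic covariates forgoes efficiency without being an error. Definitions and estimation method could indeed sit in the SAP. The protocol, however, already commits to selecting on observed difference, and that principle is what needs replacing.

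V0 also comes after allocation and group-specific consent, so the V0 scores are reported by patients who know their treatment. This stands as a caution, but the same V0 visit supplies the only pre-treatment WOMAC for the outcome itself.

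A reader might infer three stronger things that the documents do not support:

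- **That the false-positive rate is uncontrolled.** The simulation shows no material inflation under chance imbalance, with at most 5.2% even if the better of two results is kept. Systematic imbalance was not simulated.
- **That the analysis would yield an odds ratio that cannot be set against the margin.** Section 9 keeps the decision on the difference in proportions and mentions logistic regression only for predictive factors.
- **That the model would be altered by chance in 64% of trials.** That needs 20 independent variables tested at 5%, and the protocol gives neither number.

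**Conclusion.** The concern holds in a limited form. The protocol fixes a poor rule for the primary analysis: covariates chosen after looking, on undefined criteria, by imbalance and not by prognostic value, with the two scores that make up the composite included only if they differ. The consequences are a decisive model open to analyst discretion and a modest loss of precision. Against always adjusting for the two scores, the rule forgoes 81.8 - 79.3 = 2.5 or 85.6 - 80.3 = 5.3 points of power, depending on assumed prognostic strength. Against no adjustment, the gain available is about 3 to 6 points. Switching of refusers under a per-protocol analysis makes systematic imbalance plausible, but its size cannot be judged from the protocol. The change should be made before the data are analysed; the sample size is unaffected.

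**What to change.** Replace the rule in section 9 and in the summary with the following:

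1. The primary estimate is the difference in responder proportions, active minus standard, always adjusted for baseline WOMAC function and baseline VAS pain.
2. Both covariates are the pre-treatment V0 values, stated to be the same values that serve as the initial value in the composite. This settles which VAS pain reading is used, since pain is also recorded at selection.
3. A short list, named before analysis, adds already collected prognostic variables that could be related to refusing the allocation. Candidates from section 4.2 include age, professional activity, place of residence and the comorbidity index.
4. The method returns an adjusted risk difference with a 90% confidence interval, for example logistic regression with marginal standardisation, judged against -15 points.
5. The unadjusted difference, and adjustment for any other variables seen to differ, are reported as sensitivity analyses.

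The cost is a change of wording and slightly more analysis work, with no new data, visits or patients. Adjustment deals only with measured differences; it cannot remove selection by unmeasured reasons for refusal.
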